### Food samples

In contrast to pure tastes commonly used in research on gustatory perception, four ordinary, more ecologically valid mixtures of chocolate ice cream containing low vs. high levels of fatness and low vs. high levels of sweetness (Table 5) will be presented in 100-ml disposable Styrofoam cups at room temperature and in counterbalanced order across participants. Chocolate ice cream was selected according to the assumptions that chocolate ice cream is likely to be a forbidden food for AN and BN participants, and that AN participants can be expected to have strong aversive associations. The samples are stored at minus 18°C. Optimal mixtures were elaborated at the School of Agricultural, Forest and Food Sciences (Department of Food Science & Management; Bern University of Applied Sciences) and obtained considering previous studies on taste sensory and hedonic ratings (Sunday and Halmi, 1990) and surface response method (Drewnowski et al., 1987b) in AN and BN. Assuming an all-or-nothing (i.e., dichotomous) approach to food in AN and BN, regardless of the fat or sucrose levels, the specific ingredients of the samples were further selected in order to increase differences across ice cream samples in terms of sweetness, creaminess, expectation of caloric content and hedonic reactions (Table 6). In this sense, although previous studies have found pronounced aversion to the sugar-fat mixtures in AN patients, variability in aversive scores across combinations of sweet taste and fat together has also been demonstrated. For instance, differences comparing liking response profiles as a function of increasing sucrose content (0–20% wt/wt) separately from different fat samples (0.1–52.7% fat wt/wt) have been observed in AN (restrictive) and bulimic patients, and in both currently-ill and recovered patients (e.g., Drewnowski et al., 1987b; Sunday and Halmi, 1990). Finally, while water will be used as control stimulus, two savory (high-fat and low-fat) sauces will be added in study 2 as additional comparators to demonstrate that any differences detected are unique to sweet-fat foods in BN patients as previous research suggests.

**Table 5 T5:** Characterization of the food samples with low and high content of fatness and sweetness.

**Components**	**Low fatness and low sweetness**	**Low fatness and high sweetness**	**High fatness and low sweetness**	**High fatness and high sweetness**
Dry matter (%)	30.0	30.0	39.5	39.5
Fat content (%)	1.2	1.2	11.4	11.4

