In study 2, self-reports of pleasure, and facial expression responses will be characterized by a time-intensity (T-I) curve, and its constituent parameters, i.e., maximum intensity reached (Imax; 0–100), time elapsed to maximum intensity (Tmax; in seconds), and area under the curve (AUC; representing the overall emotion of the whole stimuli perceived over the total time of recording). Concerning heart rate variability, interbeat interval data will be exported to Kubios software (University of Eastern Finland, Kuopio, Finland). Inter-beat (R-R) time series will be corrected for artifacts, using a smooth priors de-trending method (λ = 500). Mean heart rate variability in terms of time and frequency domain parameters, mean skin conductance level and mean facial electromyographic amplitudes will determined before tasting food samples at baseline and thereafter.

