#### Planned analysis

Analyses will be adjusted for covariates, namely the scores of EDE-Q, BDI-II, FCQ-T-Reduced, TSF-T-Reduced, and hunger and thirst levels. Additional covariates can be added to the model if necessary. In study 1, the procedure for computing the variance of d′, confidence intervals for d', chi-square tests of significance for d′ and comparisons of multiples d′s among groups across two testing conditions will be performed for sweetness, creaminess and caloric content scores according to the Bi et al. (1997) and Bi (2008) approach. Analogous to d′, confidence intervals, hypothesis tests and multiple comparisons for C and ß will be constructed according to Kadlec's (1999) approach.

In study 2, differences in T–I parameters (Imax, Tmax, AUC), self-ratings (hedonic, familiarity) and intensity of facial expressions (emotion, valence and actions units), as well as the cardiovascular, electrodermal and facial electromyographic outcomes, will be analyzed using mixed, three-way factorial ANOVAs with group (six levels) as between-subjects and testing condition (swallowing vs. sip-and-spit) and food sample (four levels) as within-subjects' factors. Additionally, a time series emotional analysis for assessing emotional responses to beverages will be applied to automated facial expression data using the Wilcoxon signed-rank test (Crist et al., 2016) if more sensitive analysis are needed to detect differences between groups. Outcome variables will be checked for normal distribution. Note that linear mixed models to analyse the data can be envisaged to have more statistical power to detect actually existing study effects and to lead to less biased results in the case that the intraclass correlation coefficient and the design effect show dependency in the data (Hox, 1998). Statistical analyses will be conducted using SPSS (IBM, SPSS; Version 23.0, Chicago, IL, USA). Descriptive statistics will be presented using Mean ± *SD* for all continuous variables.

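### The stated Study 2 model does not use the pre-tasting baseline of heart rate variability, skin conductance and facial EMG, so resting differences can enter the direct between-group comparisons

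*Protocol article*

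**What the plan says.** Data processing (Study 2) states that mean heart rate variability, mean skin conductance level and "mean facial electromyographic amplitudes will determined before tasting food samples at baseline and thereafter". It does not say how the baseline values are then used.

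Planned analysis states that the "as well as the cardiovascular, electrodermal and facial electromyographic outcomes, will be analyzed using mixed, three-way factorial ANOVAs with group (six levels) as between-subjects" factor. Testing condition (two levels) and "food sample (four levels) as within-subjects' factors" complete the model. Adjustment is for named covariates, "namely the scores of EDE-Q, BDI-II, FCQ-T-Reduced, TSF-T-Reduced, and hunger and thirst levels". One open clause follows: "Additional covariates can be added to the model if necessary".

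Four other places bear on the point:

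- Table 2 lists the cardiovascular, electrodermal and facial EMG measures as primary outcomes of Study 2. It describes the first two in terms of changes. The EMG row speaks only of activity.
- Food samples says "while water will be used as control stimulus", and Table 4 includes water. The four food levels in the model match the four ice creams in number, so water is not stated to be a reference in the model.
- The expected results predict heart rate acceleration and higher corrugator activity in restricting-type AN, compared with three kinds of control and with BN.
- Study design concedes that the groups are not randomly assigned and not equal, and lists factors to be controlled. Resting physiology is not among them.

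**The concern.** H2 and H3 are about what happens while tasting. A reaction needs a reference level, and the plan records one for these three measures but does not place it in the model.

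The six groups differ by design in weight and illness status, so they may also differ at rest. If the response is the level after tasting begins, a group that sits higher at rest will sit higher on every sample, and this can be read as a taste reaction. The exposed tests are the direct group comparisons: AN against underweight, normal-weight and recovered controls and against BN (H2, parts 2 and 3), and the matching comparisons for BN (H3, parts 2 and 3).

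The second cost is precision. Stable between-person variation that the baseline could explain stays in the error term of those comparisons, with only 10 to 15 participants per group.

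**Working it through.** **Inputs from the Protocol article.** Group sizes per study are 15/15/10/10/15/15, with two-sided alpha 0.05 and planning effect f = 0.20 (Sample size calculation). The model has 2 conditions × 4 foods = 8 cells per person (Planned analysis).

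**Inputs assumed, because the article gives no figure.** The baseline-outcome correlation r is mainly 0.5 to 0.7. The resting difference x in one group is 0 to 1.0 SD. A pairwise effect of d = 0.8 is shown beside d = 0.4, which is what f = 0.20 means for two equal groups (d = 2f).

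**The plan's own figure.** The only power statement is N = 80 per study. The test family, number of measurements and within-person correlation are not given, so it cannot be reproduced. Nothing below depends on it.

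**Step 1: where a resting difference goes.** Let person i in group g have level a_g + u_i in every cell, plus the taste effect.

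- Group mean at a given food: contains a_g.
- Average over the 8 cells (group main effect): contains a_g.
- Difference between two foods or two conditions within a person: a_g cancels. It therefore also cancels in group × food and group × condition.

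**Step 2: false signals with no taste reaction.** For a 15 v 15 comparison of levels, the chance of p < 0.05 is the power of a two-sample t-test at d = x. Six-group simulation (stated group sizes, 8 cells, assumed between-cell correlation 0.7, resting shift in currently-ill AN only, 4,000 runs per setting):

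| Resting shift x (SD) | 15 v 15, levels (t-test) | Group main effect, levels (simulated) | Group main effect, change from baseline (simulated) |
|---|---|---|---|
| 0 | 5% | 5% | 5% |
| 0.3 | 12% | 13% | 5% |
| 0.5 | 26% | 28% | 5% |
| 0.8 | 56% | 66% | 5% |
| 1.0 | 75% | 88% | 5% |

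In the same runs, the test of group differences in a within-person contrast stayed at about 5% at every shift without any baseline. This agrees with step 1.

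**Step 3: precision.** Variance of a between-group contrast relative to analysing levels:

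- levels: 1
- change score: 2(1 − r), which is 1.0 at r = 0.5 and 0.6 at r = 0.7
- baseline as covariate: 1 − r², which is 0.75 at r = 0.5 and 0.51 at r = 0.7, so 25% and 49% are removed

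Power for 15 v 15 (non-central t, effect d/√variance, one degree of freedom lost for the covariate):

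| | Levels | Covariate, r = 0.5 | Covariate, r = 0.7 | Change, r = 0.5 | Change, r = 0.7 |
|---|---|---|---|---|---|
| d = 0.8 | 56% | 68% | 84% | 56% | 78% |
| d = 0.4 | about 18% | 23% | 32% | about 18% | 28% |

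Minimum detectable difference at 80% power is (1.960 + 0.842) × √(1/15 + 1/15) × √variance. This gives 1.02 SD for levels. The covariate gives 0.89 (r = 0.5) and 0.73 (r = 0.7). Change gives 1.02 and 0.79, but 1.21 at r = 0.3, which is worse than levels.

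**Step 4: the two corrections differ here.** With a stable resting difference x, the covariate model subtracts only r·x and leaves (1 − r)x. At x = 0.8 that is 0.40 SD (r = 0.5) or 0.24 SD (r = 0.7). Simulated false-positive rates for 15 v 15 with the covariate are then about 19–20% and 12–13%; at x = 1.0 they are about 27% and 16%. The change score stays at 5%.

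**The case against.** The best defence is that the article nowhere says absolute levels will be compared. Table 2 speaks of changes for the cardiovascular and electrodermal measures, the procedure text speaks of reactivity, and heart rate acceleration is predicted. A change score would be the outcome itself, derived at data processing, so it need not appear among factors or covariates. The open covariate clause also leaves room for the baseline, and a condensed article may leave detail to a fuller plan.

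Part of this stands. A reader might infer that the plan commits to comparing raw post-tasting levels, and the text does not support that. It supports only that the stated model does not use the baseline. None of the softer wording defines a correction, however. The listed electrodermal outcomes are a level and a rate, and the EMG row has no change wording. The open clause permits adjustment without committing to it. Nor does condensation explain the gap well: the article lists its covariates by name, gives every model factor, and reports processing detail down to the de-trending parameter.

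Two other strong readings also fail. A reader might infer that all of H2 and H3 is compromised. It is not, because the food and condition contrasts and the interactions are protected from an additive resting difference. A reader might also infer that between-person noise in these measures is known to be large. The article gives no variance or correlation, so the gain depends on r.

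**Conclusion.** The point holds in a limited form. The article records a pre-tasting baseline for three physiological measures and then states a model that does not use it as a factor level, a named covariate or part of a change score. If levels are analysed, the exposed results are the group main effect and the between-group comparisons at a given food: H2 parts 2 and 3, and H3 parts 2 and 3, for these primary outcomes.

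The sizes above are conditional. The false-positive rates require a real, additive resting difference; with none, there is no bias and only precision is lost. The simulations include none of the questionnaire or hunger and thirst covariates, which might absorb part of a resting difference. The d = 0.8 figures are illustrative. At the effect matching the plan's f = 0.20, power for a 15 v 15 comparison is low with or without the baseline (about 18% against 23–32% with the covariate). The main gain from a change score is therefore protection from misreading a resting difference. Its precision gain appears only if r exceeds 0.5.

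**What to change.** In Planned analysis, state that heart rate variability, skin conductance level and facial EMG are each analysed relative to the participant's own pre-tasting value, and fix the method before the data are seen:

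- **Between-group comparisons:** change from baseline as the response. It removes an additive resting difference fully, but loses precision if r < 0.5.
- **Sensitivity analysis:** the same model on the post-tasting value with the baseline as covariate. It is more precise, but leaves about (1 − r) of a stable resting difference. Because the groups are not randomised, the two can disagree, so both should be reported.
- **Timing:** say whether the baseline is taken once per session or before each sample. A single session baseline leaves the within-person contrasts and the interactions unchanged, so their tests need no alteration.

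The cost is a few sentences in the plan and one extra analysis per outcome. The data are already to be collected.

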#### Planned analysis

Analyses will be adjusted for covariates, namely the scores of EDE-Q, BDI-II, FCQ-T-Reduced, TSF-T-Reduced, and hunger and thirst levels. Additional covariates can be added to the model if necessary. In study 1, the procedure for computing the variance of d′, confidence intervals for d', chi-square tests of significance for d′ and comparisons of multiples d′s among groups across two testing conditions will be performed for sweetness, creaminess and caloric content scores according to the Bi et al. (1997) and Bi (2008) approach. Analogous to d′, confidence intervals, hypothesis tests and multiple comparisons for C and ß will be constructed according to Kadlec's (1999) approach.

In study 2, differences in T–I parameters (Imax, Tmax, AUC), self-ratings (hedonic, familiarity) and intensity of facial expressions (emotion, valence and actions units), as well as the cardiovascular, electrodermal and facial electromyographic outcomes, will be analyzed using mixed, three-way factorial ANOVAs with group (six levels) as between-subjects and testing condition (swallowing vs. sip-and-spit) and food sample (four levels) as within-subjects' factors. Additionally, a time series emotional analysis for assessing emotional responses to beverages will be applied to automated facial expression data using the Wilcoxon signed-rank test (Crist et al., 2016) if more sensitive analysis are needed to detect differences between groups. Outcome variables will be checked for normal distribution. Note that linear mixed models to analyse the data can be envisaged to have more statistical power to detect actually existing study effects and to lead to less biased results in the case that the intraclass correlation coefficient and the design effect show dependency in the data (Hox, 1998). Statistical analyses will be conducted using SPSS (IBM, SPSS; Version 23.0, Chicago, IL, USA). Descriptive statistics will be presented using Mean ± *SD* for all continuous variables.

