H1: If perceptual disturbances in AN and BN are related to biased cognitions about gaining weight rather than to gustatory deficits or BMI, then AN and BN patients should respond with similar sensory performance but higher response bias scores in a discrimination test, (1) compared to non-ED underweight, normal-weight and illness-recovered controls, and (2) during a swallowing compared with a sip-and-spit condition.H2: If fear of weight-gain in restricting-type AN elicits taste aversion, then facial electromyographical, facial expression, and autonomic and subjective correlates of disgust (Kappas, 2003; Kreibig, 2010) while tasting high-sweet and high-fat foods should be observed compared to (1) stimuli of low-sweet and low-fat foods; (2) non-ED underweight, normal-weight, illness-recovered controls and (3) BN patients; and (4) especially during the swallowing compared with the sip-and-spit condition.H3: If avoidance of energy-rich foods in BN reflects a cognitive preoccupation about the increased liking of very sweet tastes associated with gaining weight, then facial electromyographical, facial expression, and autonomic and subjective correlates of pleasure (Kappas, 2003; Kreibig, 2010) while tasting high-sweet foods should be observed compared to (1) fat and low-sweet stimuli; (2) non-ED underweight, normal-weight, illness-recovered controls and (3) restrictive-type AN; and (4) no differences between swallowing and sip-and-spit conditions.

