**Current anorexia and bulimia nervosa groups**
Diagnoses of AN (restricting-type without previous history of binge-eating/purging type) or BN (without history of AN)
If treatment has started, reduction of the initial eating disorder pathology measured by EDE-Q (Mond et al., 2004) <30%.
<50% of the target weight gain (AN) or <30% reduction of binge eating and compensatory episodes (BN)

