**Recovered anorexia and bulimia nervosa groups**
Not meeting all criteria for an AN or BN at the time of discharge
BMI > 18 and a global EDE-Q-score <2.3 (Munsch, 2014)

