**Figure 2 F2:**
[figure not shown]
Flow graph of the procedure.

**Table 2 T2:** Summary of the measures, instruments and outcomes.

**Type**	**Measure/instrument**	**Measure description**	**Device/author**	**Outcome**	**Study**
Subjective	Diagnostic interview for psychiatric disorders (**Mini-DIPS**) and Structured Clinical Interview for DSM-IV (**SCID-I**)	Structured interviews to assess psychiatric disorders according DSM-IVTR and DSM-5	Wittchen et al., 1997; Schneider and Margraf, 2011	Diagnostic phase	Study 1 & 2
	Eating Disorder Examination Questionnaire (**EDE-Q**) (score)	36 items scored on a 7-point Likert-type scale reporting restraint, eating concerns, weight concerns and shape concerns, as well as frequencies of compensatory behaviors are also self-reported. Internal consistency >0.70; test-retest reliability >0.50	Mond et al., 2004	Diagnostic phase	Study 1 & 2
	Thought-Shape Fusion Body State Scale (**TSF-B state**)	5-item questionnaire assessing body-related cognitive distortions according to Radomsky et al., 2002. Each item rated on a 100-mm VAS scale (0–100). Cronbach's alpha = 0.86	Wyssen et al., 2016	Baseline	Study 1 & 2
	Beck Depression Inventory-II (**BDI-II**) (score)	21 items rated in a 3-point scale indicates depression raging from normal mood to severe depression. Internal consistency >0.90; test-retest reliability >0.90; convergent validity >0.71	Beck et al., 1996	Baseline	Study 1 & 2
	Food Cravings Questionnaire—Trait (**FCQ-T-reduced**) (score)	15 items scored on a 6-point scale related with eating pathology, body mass index, low dieting success and increases in state food craving during cognitive tasks involving appealing food stimuli. Internal consistency >0.70; validity demonstrated by positive correlations between scores on the FCQ-T-r, BMI and cue-elicited FC; convergent validity >0.50	Meule et al., 2011	Baseline	Study 1 & 2
	Thought-Shape Fusion Questionnaire (**TSF-Trait**) (score)	18 items which measures the susceptibility to body-related cognitive distortions	Coelho et al., 2013; Wyssen et al., in press	Baseline	Study 1 & 2
	The Brief Mood Scale (**BMS**)	8 bipolar items on a 100-mm VAS (0–100). Cronbach's alpha >0.88	Wilhelm and Schoebi, 2007	Baseline	Study 1 & 2

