### Study design

The present international and multi-center research uses a quasi-experimental, cross-sectional design with concurrent controls aims at comparing gustatory perception and hedonics of taste among six groups of participants: R-AN, C-AN, U-CT, N-CT, R-BN, and C-BN, under two counterbalanced conditions of testing: sip-and-spit vs. swallow test condition. The use of a rigorous quasi-experimental design with a well-established type of psychopathology represents an important approach in the experimental psychopathology literature (Zvolensky et al., 2013), particularly in the context of eating disorders for both ethical and pragmatic reasons. However, the limitations are related to the lack of random assignment into groups, which leads to non-equal test groups, which can limit the generalizability of the results to a larger population. In order to reduce the impact of this limitation, threats to validity will be minimized controlling the following factors: comorbidity, stage-of-illness, age-at-onset, duration of illness and time in treatment, depressive mood, craving for food, biased cognitions about weight, current hunger, thirst and food familiarity. In addition, age-matched and weight-matched controls (to the extent possible) will be included in the research design to increase the chances of finding differences between groups. Additional controls by limiting our inclusion criteria are not envisaged as this would make it even more difficult to obtain samples of adequate size (therefore reducing statistical power) and limiting the generalizability (and hence the external validity) of the study protocol.

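### Adjusting every analysis for EDE-Q and TSF-Trait biases towards null the between-group differences that H1 (C and ß) and H2 predict

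*Protocol article*

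**What the plan says.** The protocol article, Planned analysis, opens with a rule that covers both studies: "Analyses will be adjusted for covariates, namely the scores of EDE-Q, BDI-II, FCQ-T-Reduced, TSF-T-Reduced, and hunger and thirst levels". The Study design section gives the motive. The groups are not randomised, so a list of factors will be controlled to protect validity, and that list includes "biased cognitions about weight, current hunger, thirst and food familiarity".

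Elsewhere the same variables have other roles:

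- **Entry criterion.** Table 1 requires recovered participants to have "BMI > 18 and a global EDE-Q-score <2.3". For currently-ill patients EDE-Q enters only conditionally: "If treatment has started, reduction of the initial eating disorder pathology measured by EDE-Q" must be below 30%.
- **Mechanism.** H1 is conditional on a cause: "If perceptual disturbances in AN and BN are related to biased cognitions about gaining weight rather than to gustatory deficits or BMI". H2 begins "If fear of weight-gain in restricting-type AN elicits taste aversion". Figure 1A places weight-related cognitions upstream of taste aversion in restricting AN.
- **Measurement of that mechanism.** Table 2 describes the TSF-Trait as "18 items which measures the susceptibility to body-related cognitive distortions", and lists weight and shape concerns among the EDE-Q content.

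The section on expected results names the confirming findings. They are lower C and ß in currently-ill patients than in recovered patients and controls, similar d′, and, in AN, lower ratings with higher corrugator activity, disgust expressions and heart rate acceleration.

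**The concern.** A covariate is useful when it is a nuisance to the comparison. Here two of the listed covariates are close to the comparison itself. EDE-Q separates recovered from ill partly by rule, and can be expected to track current illness in the other groups. TSF-Trait is the study's measure of the biased cognition that is supposed to produce the group difference. Holding it fixed asks whether AN patients differ from controls who have the same degree of cognitive distortion, which is not what H1(1) or H2(2) asks.

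Two consequences follow. If H1 or H2 is true, the adjusted group contrast shrinks in proportion to the share of the effect that the covariates carry, and the shrunken result would be read as evidence against the hypothesis. Even if they carry none of it, their correlation with group widens the standard error. For d′, where H1 predicts no group difference, a wider interval makes a finding of similarity easier to reach and less informative.

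**Working it through.** The plan gives no figure for the effect of adjustment, so there is none to reproduce. Its 80 participants per study is used below only for the group sizes.

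**From the Sample size calculation section:** per study, C-AN 15, C-BN 15, R-AN 10, R-BN 10, U-CT 15, N-CT 15 (80 in all); two-sided alpha 0.05.

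**Assumed, because the protocol does not give them:** C-AN vs N-CT difference of 1.06 within-group SD; one covariate whose C-AN and N-CT means differ by Δ = 1, 2 or 3 within-group SD; a share s = 0, 0.5 or 1 of the effect running through it; residual SD 1. TSF-T-Reduced in the covariate list is taken to be the TSF-Trait of Table 2 or a short form of it.

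**Unadjusted:** SE = √(1/15 + 1/15) = 0.365; 1.06/0.365 = 2.90 on 74 df; power about 82%.

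**Adjusted:** expected estimate = (1 − s) × 1.06, that is 1.06, 0.53 or 0. SE = √(2/15 + Δ²/74), where 74 = 80 − 6 is the expected within-group sum of squares of the covariate in SD units.

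| Δ | SE | power, s = 0 | power, s = 0.5 | power, s = 1 |
|---|---|---|---|---|
| 1 | √(0.1333 + 0.0135) = 0.383 | 78% | 28% | 5% |
| 2 | √(0.1333 + 0.0541) = 0.433 | 68% | 23% | 5% |
| 3 | √(0.1333 + 0.1216) = 0.505 | 54% | 18% | 5% |

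A simulation at Δ = 3 (2000 runs per scenario) gave SE 0.51 and power 53%, 18% and 5%, in agreement.

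**Sensitivity to the residual SD.** If the total within-group SD is held at 1 instead, a covariate that carries half the effect also explains residual variance. At Δ = 1 the slope is 0.53, the residual SD is √(1 − 0.53²) = 0.848, the SE is 0.325 and power is about 36% instead of 28%. At Δ = 3 power stays at about 18%.

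**A second contrast.** Currently-ill vs the other four groups, assumed difference 0.7 SD, total within-group SD 1, Δ from 1.0 to 2.5, 4000 runs per cell. Unadjusted SE was 0.23 and power 0.84–0.85. Adjusted power was 0.74 down to 0.45 with s = 0 (SE 0.26 to 0.37), 0.28 down to 0.15 with s = 0.5, and 0.05 with s = 1.

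**Precision for a predicted null.** On the same scale, the 95% half-width for C-AN vs N-CT goes from 1.99 × 0.365 = 0.73 SD to as much as 1.99 × 0.505 = 1.0 SD at Δ = 3. This applies to d′ if it is adjusted in a model of this form.

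**What is exposed.**

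- *Between-group predictions:* H1(1) for C and ß, H2(2) and H2(3) are exposed to the extent that the covariates differ between the groups compared and carry the effect. Group interactions with condition or food are exposed to the same extent.
- *Average within-person predictions:* H1(2), H2(1) and H2(4), as average differences between conditions or foods, are not removed, because a person-level score is the same in both conditions.

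**The case against.** The strongest counter-arguments, and what stands of each:

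- **H3 does not fit the mechanism argument.** This stands. In Figure 1B the weight cognitions oppose intake and do not produce the pleasure response; H3 predicts no swallow–spit difference. Craving is not drawn as a step from diagnosis to taste response, so calling FCQ-T a mediator there is inference. What remains for H3 is collinearity with group.
- **The design already tests cognition through the swallow condition.** This stands in part. The Procedure section includes swallowing to strengthen and quantify the cognitive influence, and that within-person test survives adjustment. It does not rescue the between-group predictions.
- **EDE-Q does not define all the groups.** This stands. Currently-ill patients enter by DSM-5 diagnosis, and the EDE-Q rule limits change in those already treated. Controls enter by no eating-disorder history and BMI. Only the recovered groups have a score cut-off.
- **Study 1 names no regression model.** This stands as a limit on the numbers. The article names chi-square comparisons of d′ and analogous procedures for C and ß, so the least-squares calculation illustrates the loss and does not measure it for Study 1. The direction of the bias follows from the adjustment itself.
- **A vanishing adjusted effect would support mediation.** The expected-results section treats group differences as the confirming findings, so the stated reading of a null would be the opposite.
- **A fuller plan may contain unadjusted or mediation analyses.** It may, and their absence from the article is not counted here. The point is the rule that the article does state, without exception.

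A reader might infer that the adjustment wipes out every effect the study seeks. The documents do not support that, for the reasons above.

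**Conclusion.** The concern holds for the between-group predictions of H1 (C and ß) and H2. The stated adjustment conditions on the recovered groups' entry score and on the measure of the hypothesised cause, so it biases those contrasts towards null and inflates their standard errors. It also weakens the predicted similarity of d′. The direction rests on the protocol's own definitions and hypotheses.

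The size is conditional. With the planned n, a 1.06 SD difference, residual SD 1 and a separation of 1 to 3 SD, power falls from about 82% to about 78–54% with no mediation and about 28–18% with half. The contrast goes to zero, and power to 5%, only if the covariates carry the whole effect; that is one end of the range and not a certainty. None of the separations, shares or effect sizes is in the protocol, and the calculation uses one covariate where the plan lists several. The change is worth making before analysis, because otherwise the main group comparisons do not answer the stated hypotheses.

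**What to change.** Reword the Planned analysis section so that:

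1. The primary group comparisons in both studies omit EDE-Q, TSF-Trait and FCQ-T, and keep pre-tasting hunger and thirst.
2. The fully adjusted model is reported as secondary, described as the group difference at equal trait scores.
3. The cognition claim is tested in a separate, pre-stated analysis, for example by relating each participant's swallow-minus-spit difference to TSF.

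The Study design list of controlled factors should then say that biased cognitions about weight are examined as a mechanism and are not adjusted away in the primary comparison. Whether BDI-II stays in the primary model is for the investigators to decide; the defect described here does not settle it.

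The cost is wording only, with no change to recruitment, measures or sessions. The downside is that group differences in these traits are dealt with in the secondary model, so the primary contrast describes the groups as they are, with the confounding that a non-randomised design carries.
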